1$$ {\displaystyle \begin{array}{l}{Y}_i={X}_i{\theta}_i+{\varepsilon}_i\kern0.5em \mathrm{with}\kern0.5em {\varepsilon}_i\sim N\left(0,{\Sigma}_i\right)\\ {}{\theta}_i\sim N\left(\theta, D\right)\end{array}} $$where *Y*_*i*_ = (*Y*_*i1*_, *Y*_*i2*_, …, *Y*_*ij*_) denotes the *i*-th (*i* = 1, 2, …, *n*) subject’s response value for the *j*-th (*j* = 1, 2, …6) period; *θ*_*i*_ follows a multivariate normal distribution with mean *θ* and a covariance matrix *D*. *θ*_*i*_ contains treatment effect (μ_i_) between mesalazine and modified SJZD. When *μ*_*i*_ is same for each patient (*μ*_*i*_ *= μ*), it is a fixed effect. If *μ*_*i*_ varies across different patients, it is a random effect. Some covariance structures for the random error are assumed, including: (1) compound symmetry (common variance across patients with uncorrelated and identically distributed errors), (2) first-order autoregressive, and (3) unstructured: which may be overparameterised. In these models, other factors (carryover effects and period effects) are also considered. The mixed models are fitted using the ‘lme4’ package in R software (version 3.6.2). Different models are compared using the Bayesian information criterion (BIC) [35]. Finally, we prefer the model with the lowest BIC.

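### Two of the three error covariance structures to be compared by BIC cannot be fitted in the named package (lme4), and the third is mislabelled

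*Protocol article*

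**What the plan says.** The Statistical methods section of the protocol article pools the patients with a paired t test and, because the data are correlated, also with a mixed model. The model has an error term with covariance Σ_i and, separately, patient-level effects with covariance D. The list of structures is attached to the error term: "Some covariance structures for the random error are assumed, including". The first is "compound symmetry (common variance across patients with uncorrelated and identically distributed errors"; the others are "first-order autoregressive, and (3) unstructured: which may be overparameterised". Carryover and period effects are also considered. The software is fixed: "The mixed models are fitted using the ‘lme4’ package in R software". So is the choice of model: "Different models are compared using the Bayesian information criterion (BIC", and "we prefer the model with the lowest BIC". No other package is named for this step.

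**The concern.** The package, the candidate structures and the selection rule are all stated, and they do not fit together. Correlated errors need software that can model Σ_i, whereas `lmer` treats errors as independent given the random effects. The first candidate has a different fault: compound symmetry means a constant within-patient correlation, but the bracket describes uncorrelated errors.

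The mixed model carries weight in this trial. There is no washout, and the Discussion relies on the model to separate carryover from treatment. If the listed comparison cannot be run, the analyst must change package or drop candidates, possibly after seeing the data, or else report the independent-error model as though it had won a comparison that never took place.

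**Working it through.** **Inputs.** Three cycles of two periods give 6 measurements per patient (Trial design; Outcomes). Ten patients (Sample size) give 10 × 6 = 60 observations. Order is AB or BA, randomised within each cycle (Randomisation, treatment allocation, and blinding).

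**1. Can `lmer` take the structures?** The check used lme4 1.1-37. `lmer` has no correlation argument, and passing `corAR1` stops with an unused-argument error. `nlme::lme` has such an argument.

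**2. Can random effects stand in for them?**
- *AR(1).* The model was a random intercept plus random treatment effect with independent errors, for the sequence AB BA AB. Its closest least-squares match to an AR(1) matrix, on a unit-variance scale, misses an element by 0.19 (ρ = 0.3), 0.27 (ρ = 0.5) or 0.34 (ρ = 0.7).
- *Unstructured.* The nearest form, `(0 + period | id)`, is refused: 60 observations against 60 random effects leave the residual variance unidentified. A free 6 × 6 matrix has 6 × 7 / 2 = 21 parameters. One random-intercept variance makes 22 parameters for 21 distinct marginal elements.

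**3. What can be fitted?** A random intercept with variance τ² and independent errors with variance σ² give covariance τ² between any two periods and variance τ² + σ² in each. That is compound symmetry in the marginal covariance. On one simulated data set `lmer` with a random intercept and `nlme::gls` with compound symmetry gave the same log-likelihood, −75.28045.

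**4. Is the comparison possible elsewhere?** `nlme::gls`, without random effects, fitted all three structures in 200 of 200 simulated 10 × 6 data sets. In the first, compound symmetry, AR(1) and unstructured had 9, 9 and 28 parameters and BIC 184.4, 188.7 and 226.5. Those data were generated with a random intercept and independent errors, so the ranking shows only that the comparison runs.

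**5. What does fitting only independent errors do?** Let the errors be AR(1) with variance σ² and correlation ρ, and the treatment effect common to all n patients.
- A within-cycle difference has variance 2σ²(1 − ρ). Order is randomised independently in each cycle, so covariances between cycles average out. The true variance of the estimate is 2σ²(1 − ρ)/(3n).
- The independent-error model with patient effects uses about σ²(1 − r̄) as its residual variance, where r̄ = Σ(6 − k)ρ^k / 15 for k = 1 to 5. It reports about 2σ²(1 − r̄)/(3n).
- The reported standard error is therefore too large by a factor √[(1 − r̄)/(1 − ρ)], and null rejection is about P(|Z| > 1.96 × factor).

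| ρ | r̄ | Variance ratio | SE factor | Null rejection |
|---|---|---|---|---|
| 0.3 | 0.131 | 1.24 | 1.11 | 2.9% |
| 0.5 | 0.269 | 1.46 | 1.21 | 1.8% |
| 0.7 | 0.476 | 1.75 | 1.32 | 1.0% |

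Simulations of 10 patients, with differing adjustments and reference distributions, gave 2.3% to 3.7%, 1.8% to 2.3% and 1.0% to 1.5% at these three correlations. With a carryover term the loss is smaller: about 4.2%, 4.0% and 3.3%. A paired t test on the 30 within-cycle differences stayed between 4.7% and 5.2%.

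**6. Is the sample size touched?** The plan's figure is 8, raised to 10. With SD 0.8, difference 0.7 and three cycles, a t test on 3n differences with variance 2 × 0.8² has power 76.9% at n = 7 and 82.7% at n = 8; 8 / 0.8 = 10. The error structure for the mixed model does not enter.

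**The case against.** The strongest defence is that the damage is small. The model with independent errors fits in lme4 and yields marginal compound symmetry, so the first candidate is available under a loose label and no estimate changes. The plan itself warns of the third candidate, "unstructured: which may be overparameterised", and BIC penalises it heavily, so losing it is unlikely to alter the choice. The trial is sized on a common treatment effect, and a pooled paired t test survives. All of this stands, and it limits the consequences. It does not make AR(1) fittable, and AR(1) is the candidate that addresses serial dependence over six consecutive periods.

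A reader might infer three stronger things that the documents do not support.
- *The mixed model cannot be fitted at all.* It can, with independent errors.
- *Ignoring serial correlation inflates the false-positive rate.* Under within-cycle randomisation and positive correlation the effect runs the other way.
- *The type I error is about 8%.* That is P(|t| > 1.96) = 0.082 on 9 degrees of freedom, which needs both a z reference and a treatment effect that varies between patients. The plan states no z test. With a common effect the degrees of freedom are 60 − 10 − 1 = 49, or 44 with five period terms, and the figure is 5.6%. How P values and degrees of freedom are obtained is ordinary analysis-plan detail, and its absence from an article is no fault.

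**Conclusion.** The point holds as a mismatch between software and model, together with a mislabelled structure. Two of the three candidates cannot be specified in the named package, so the BIC selection cannot be carried out as written. The statistical cost arises if errors are positively autocorrelated: the standard error is overstated by about 11% to 32% for ρ from 0.3 to 0.7, with a corresponding loss of power in a trial planned on 8 evaluable patients.

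This rests on three assumptions. The documents do not give ρ, so the range is illustrative. The figures assume a common treatment effect and no carryover term. The documents give the R version but no lme4 version, so the release used with R 3.6.2 is assumed to behave like the one checked.

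**What to change.** Before unblinding:
1. Replace lme4 for this step with software that models residual correlation, for example `nlme::lme` or `nlme::gls` with `corAR1` over period.
2. Either define compound symmetry as a constant within-patient correlation, or say that the label refers to the marginal covariance produced by a random patient intercept with independent errors.
3. Drop the unstructured option. Its 21 parameters are not identifiable alongside random patient effects with 10 patients and 6 periods.
4. Keep the lowest-BIC rule for the candidates that remain.

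The cost is a few lines of code and wording. Design, data collection and sample size do not change, and the pooled paired t test can stay as planned.

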## Discussion

A sufficient washout period is necessary for *N*-of-1 trials because the latter intervention may be affected by the carryover effects of the previous intervention. However, the patient does not receive effective treatment during washout periods. Therefore, including a washout period would be inappropriate for UC patients. For patients with UC in the remission phase, insufficient treatment leads to acute UC or aggravation of UC [36, 37]. Therefore, there are no washout periods in our study.

Although there are no washout periods in this study, we considered that the carryover effects of modified SJZD have little effect in practice. The reasons are as follows: (1) the main active ingredients of SJZD are glycyrrhizic acid, glycyrrhetinic acid, pachymic acid, atractylodes lactone III, ginsenoside Re, and ginsenoside Rb_1_, and a pharmacokinetic study showed that their mean half-life is no more than 12 h [38]. For the other active ingredients of modified SJZD, further studies reported that their half-life is no more than 24 h [39–45] and (2) even if there are carryover effects for modified SJZD, a mixed-effect model will be used to analyse the data from the *N*-of-1 trials. The mixed-effects model can estimate treatment effects accurately while controlling for carryover effects; it separates carryover effects from treatment effects in a series of *N*-of-1 trials [34].

The Mayo score is a general indicator used to assess the severity of active UC [6]. If the procedure for calculating the Mayo score is followed properly, the patients with UC would undergo enteroscopy after each period (one per month in the trial). This would be too frequent for patients to accept. Therefore, the Mayo score will not be used as the primary outcome. Diarrhoea, abdominal pain, and mucus in the stool are the most common symptoms for patients with UC. Bloody purulent stool was reported to have a close relationship with clinical relapse [46, 47]. For these reasons, the VAS scores for the main clinical symptoms (diarrhoea, abdominal pain, mucus in the stool, and bloody purulent stool) were chosen as the primary outcomes.

Our findings will be interpreted with caution. We anticipate that the results will show that modified SJZD is effective for patients with UC in remission.

### Trial status

The recruitment will begin on 1 March 2020, and we expect this study to be completed by 30 February 2022.

## Data Availability

The data used to support the findings of this study will be available from the Chinese Clinical Trial Register (ChiCTR1900024086) within 6 months after the trial is complete.

## Abbreviations

UC: Ulcerative colitis
QOL: Quality of life
TCM: Traditional Chinese medicine
SJZD: *Sijunzi* decoction
*N*-of-1: Single-case randomised controlled
RCT: Randomised controlled trial
GZUCM: Guangzhou University of Chinese Medicine
CENT: CONSORT extension for reporting *N*-of-1 trials
VAS: Visual analogue scale
SIBDQ: Short Inflammatory Bowel Disease Questionnaire
RFIPC: Rating Form of Inflammatory Bowel Disease Patient Concerns
SHS: Short Health Scale
APAGE: Asia Pacific Association of Gastroenterology
CRF: Case report form
